## Outcomes

Primary outcome measures: 1a) a between-group difference in gut microbial alpha diversity will be measured using Shannon diversity index at the 7th day and 1b) a between-group difference in the concentration of fecal metabolites (short chain fatty acids) will be quantitatively measured using non-targeted liquid chromatography-mass spectrometry (LC–MS) at the 7th day.

Secondary outcome measures: 2a) between-group differences in other diversity indicators of gut microbiota, including Simpson index (an indicator of species richness and evenness less affected by rare species than Shannon index) and Chao1 index (estimated total number of species) at the 7th day; 2b) between-group differences in alpha diversity of gut microbiota measured using Shannon index, Simpson index and Chao1 index on the 14th, 21st and 28th days of life; 2c) Between-group differences in the concentration of fecal metabolites quantitatively measured by non-targeted LC–MS at the 14th, 21st and 28th days of life; 2d) proportion of gut microbiota at phylum and genus level; 2e) gut microbial beta diversity explaining between-sample dissimilarity calculated using the Vegan package; and 2f) correlation between the comparative dominant flora and metabolites (Table 1).

**Table 1 Tab1:** Outcomes, measures and methods of analysis

Outcome	Hypothesis	Outcome Measure	Methods of Analysis
**1.Primary** 1a A between-group difference in Shannon diversity index at the 7th day	OAC increases Shannon diversity and metabolites of gut microbiota	Shannon index (continuous)	Individuals: Wilcoxon text; Intergroup: T/Wilcoxon text
1b A between-group difference in fecal metabolites at the 7th day		Short chain fatty acids (continuous)	Individuals: FC, PCA/PLS-DA Intergroup: T/Wilcoxon text
2.** Secondary** 2a Between-group differences in other alpha diversity indexes (Simpson, Chao1) at the 7th day	OAC increases other alpha diversity and beta diversity, and changed the proportion of gut microbiota from birth to day 28. There is a Correlation between dominant microbiota and metabolites	Simpson index, Chao1 index (continuous)	Individuals: Wilcoxon text; Intergroup: T/Wilcoxon text
2b Between-group differences in Shannon index, Simpson index and Chao1 index at the 14th, 21st and 28th days of life		Shannon index, Simpson index, Chao1 index (continuous)	Individuals: Wilcoxon text; Intergroup: T/Wilcoxon text

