### Randomization

A 1:1 block randomization scheme will be adopted. Each group will be stratified by birth gestational age (< 28 weeks, 28 weeks, and 32 weeks). A random serial number will be randomly generated for each layer using SAS (v9.4 SAS Inst. Inc., Cary, NC) before the start of the study. The block length will be 6. Statisticians will prepare sealed, numbered, opaque envelopes for each site and hand them over to the study coordinator, who will ensure that the envelopes are used in a numerical order. After receiving the notice, the study coordinator will open the envelope, take down the group assignment form, copy the form and send it to the statistician. The manuscript will be left in the case file of the preterm infant. To achieve blinding, the study coordinator preparing the syringe (colostrum or placebo) will be different from the nurse conducting the intervention. The subjects, intervention nurses, the principal investigator and the data verifier will be blinded. During the pilot test, non-fixed codes will be used for blinding to represent each allocation scheme to prevent unblinding by inadvertently losing blindness to all trial participants.

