**Fig. 2 Fig2:**
[figure not shown]
Quality control process of the protocol. DMC, data monitoring committee (composed of data verifiers at the coordination center and the principal investigators at each center); CRF, case report form. * The research team of each center is composed of the principal investigator, data quality controller, syringe preparing nurse and the intervener. ** The trial steering committee (composed of the directors of neonatal pediatrics at each center and the heads of the medical safety review team)

The whole research team will hold online meetings every month through multimedia video conferencing software to discuss the implementation of the scheme as needed and quickly solve any problems. When 50% of randomly assigned patients completed five stool samples collection, the primary endpoint was analyzed in the interim. An interim-analysis will be conducted by independent statisticians without knowledge of treatment allocation. Statisticians will report to the DMC. The DMC will conduct non-blind access to all data and discuss the results of the interim analysis, adverse events and compliance with the trial steering committee (composed of the directors of neonatal pediatrics at each center and the heads of the medical safety review team) at the multicenter meeting. Adverse events are defined as aspiration to the lungs, resuscitation due to severe bradycardia or apnea after intervention, and postnatal infection with cytomegalovirus thought to be associated with fresh breast milk. If cases related to these adverse events occur, we will intervene immediately. To ensure the safety of the included infants, vital signs will be carefully monitored during oropharyngeal administration. If the vital signs are unstable, the intervention will be stopped in time. The trial steering committee will decide to continue the trial and report to the ethics committee, which is independent of the sponsor and investigators (Fig. 2).

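### A data monitoring committee with non-blind access is to discuss the interim results with the neonatal directors of every recruiting centre, so comparative results may reach those units while infants are still being enrolled

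*Protocol article*

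**What the plan says.** Four statements in the text after Fig. 2 (Quality control) set the route of the interim results.

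- Timing and content: "When 50% of randomly assigned patients completed five stool samples collection, the primary endpoint was analyzed in the interim".
- Analysis: "An interim-analysis will be conducted by independent statisticians without knowledge of treatment allocation". These statisticians report to the DMC.
- Access: "The DMC will conduct non-blind access to all data".
- Onward sharing: the DMC is to "discuss the results of the interim analysis, adverse events and compliance with the trial steering committee (composed of the directors of neonatal pediatrics" and others). The full membership is the "directors of neonatal pediatrics at each center and the heads of the medical safety review team".

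The steering committee then acts on what it has heard: "The trial steering committee will decide to continue the trial and report to the ethics committee". The Sample size section adds that the sample size will be adjusted on the interim results.

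Two other sections bear on this. Outcomes defines the first primary outcome as "a between-group difference in gut microbial alpha diversity will be measured using Shannon diversity index at the 7th day", and the second, on short chain fatty acids, is also a between-group difference. Randomization states: "The subjects, intervention nurses, the principal investigator and the data verifier will be blinded".

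**The concern.** The trial is described as double-blind. Interim comparisons are normally confined to a small group with no hand in running the trial, so that the rest of enrolment proceeds without knowledge of a trend. Here the stated route carries the interim discussion to the neonatal directors of all the recruiting centres, and the committee they sit on also decides whether the trial continues.

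If those discussions include the comparison between arms, knowledge of a trend could affect which families are approached, how hard retention is pursued, and co-interventions in the units. The protocol itself (Statistical analysis and Discussion) names antibiotic use and feeding type as influences on the gut microbiota. It could also colour the continuation and sample size decisions.

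This is separate from the question of who sits on the DMC. Replacing its members would leave the sharing rule as it stands.

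**Working it through.** **Step 1. Does the route carry comparative results?** Reading the statements in order:

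1. The interim analyses the primary endpoint (Quality control).
2. Both primary outcomes are between-group differences (Outcomes), so a result on the primary endpoint is by nature a comparison of arms.
3. The interim statisticians do not know the allocation, but they report to a DMC that has non-blind access. The mask ends there.
4. The DMC discusses the results with the steering committee, and no restriction on their form is stated.

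The text never says that results are shown by arm. That they may be is an inference from items 1 to 4.

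**Step 2. Are the recipients at the recruiting centres?** Yes. The committee includes the neonatal director of each centre, so all three centres are reached.

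**Step 3. Are infants still to be enrolled?** First, the plan's own total. For a difference of 0.2 and SD of 0.6, with two-sided alpha 0.05 and 80% power, the normal formula gives 2 × (1.960 + 0.842)² × 0.6² / 0.2² = 141.3, so 142 per group. The t-based solution is 142.2, rounded up to the stated 143. Dividing by 0.90 and 0.88 for 10% and 12% loss gives 159 and 163, which bracket the stated 160 per group (320 in total). The total reproduces.

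Inputs from the article: 320 infants enrolled within one year (Abstract); trigger at 50% with all five stools, the last on day 28. Assumptions, not in the article: even accrual, the 50% taken as 160 of the planned 320, no losses, and the delay from trigger to meeting.

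- Accrual rate: 320 / 12 = 26.7 infants per month.
- 160th infant enrolled: 160 / 26.7 = month 6.0.
- Day-28 stool: 28 / 30.4 = 0.92 months later, so the trigger is at about month 6.92.
- Enrolled by then: 26.7 × 6.92 ≈ 185.

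| Meeting after trigger | Month | Enrolled | Still to enrol |
|---|---|---|---|
| 0 months | 6.92 | 185 | 135 (42%) |
| 1 month | 7.92 | 211 | 109 (34%) |
| 2 months | 8.92 | 238 | 82 (26%) |

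Losses before day 28 would delay the trigger and lower these counts.

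**Step 4. Would a closed DMC report suffice?** Not as the DMC is now constituted. Quality control and the Fig. 2 legend make it up from the data verifiers and the principal investigators at each centre. Randomization says that the principal investigator and the data verifier are blinded. A report closed to everyone but the DMC would still leave comparative results with centre staff who are meant to be blinded.

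**The case against.** The strongest objection is about form. The article says the results are discussed and does not say how they are presented. Non-blind access is given to the DMC, not to the steering committee, and the masked statisticians could report by coded group. This stands against any claim that by-arm results will reach the directors. It does not remove the risk, because the unblinded body leads the discussion and nothing limits it.

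A second objection is that open and closed sessions usually belong in a DMC charter, which a journal article may omit. That is right as far as silence goes. The point here rests on a rule the article does state: the results are discussed with this committee.

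A third concerns harm, and much of it stands:

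- A reader might infer that the directors control enrolment, feeding and antibiotics. The article names them only as committee members. It places lactation education in obstetrics and has the principal investigator explain the study to mothers.
- A reader might infer a contradiction with the blinding statement. The directors are not on its list. The contradiction concerns the principal investigators and data verifiers on the DMC.
- An aggregate trend does not reveal any infant's arm, and the intervention nurses are blinded, so a unit-wide change in practice would tend to fall on both arms. Both primary outcomes are laboratory measures, which limits assessment bias. Against this, each centre's team includes a syringe preparer who handles colostrum or water and so knows the allocation.

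A last objection is that, while centre principal investigators sit on an unblinded DMC, telling the directors as well adds little. That is a reason to correct both together.

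**Conclusion.** The concern holds in a measured form. The article states a route by which comparative interim results may reach the neonatal leadership of all three recruiting centres during enrolment. Under even accrual over 12 months, about 135 infants (42%) would still be to enrol at the trigger, and 109 to 82 (34% to 26%) if the meeting follows one to two months later. The accrual pattern, the reading of the 50% trigger, the absence of losses and the meeting delay are all assumptions.

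Two stronger statements are not supported. A reader might take the 160 infants beyond the 50% mark as all exposed. That is a ceiling, since about 25 of them (185 − 160) would already be enrolled at the trigger and many would be past the day-7 primary sample. A reader might also conclude that the second half of the trial would be damaged beyond repair. Randomisation within each period still stands, and a comparison before and after the interim could look for a shift, although it could not remove one. The size of any bias cannot be calculated from the article.

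**What to change.** Amend the paragraph after Fig. 2 in Quality control so that:

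- comparative interim results stay in a closed DMC report;
- the steering committee receives only a written recommendation on the conduct of the trial, plus pooled (not by-arm) data on recruitment, compliance and adverse events;
- the steering committee keeps its decision on continuation and takes it on that recommendation.

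In the same amendment, reconcile Randomization with Quality control and the Fig. 2 legend, so that the centre principal investigators and data verifiers, stated to be blinded, do not hold the non-blind access. Without this the closed report does not protect the centres.

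The cost is one paragraph of wording, an open and closed split of a report already planned, and assigning the non-blind access to people other than those stated to be blinded. The downside is that centre directors see less at mid-trial. The arrangements for responding to adverse events in individual infants are not touched. The change should be in place before the interim.

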**Discussion:**

This proposal advocates for the promotion of OAC as a safe and relatively beneficial protocol in neonatal intensive care units, which may contribute to the establishment of a dominant intestinal flora. Findings of this study may help improve the health outcomes of preterm infants by establishment of targeted gut microbiota in future studies.

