### Data collection

Descriptive and clinical data be collected from both groups. Birth status characteristics, such as delivery mode, gestational age, weight and length, Apgar score will be collected in addition to the mothers’ occupation, education level, disease, use of drugs, supplements and antibiotics. During hospitalization, clinical data will be collected on enteral feeding (start time, duration, starting dose, feeding type and total enteral feeding time); parenteral nutrition (start time and duration); antibiotics use in infants (type, start time, duration and dose); NEC, LOS and mortality; and respiratory support.

We hypothesize that OAC would regulate gut microbiota and its metabolites in very preterm infants, resulting in an increase in microbial diversity, with increasing dominance of Lactobacillus/Bifidobacterium predominating and a relative decrease in Proteus species. Stool samples will be collected from selected subjects at the first defecation, as well as on the 7th, 14th, 21st and 28th days and immediately frozen at − 80 °C. Fecal samples refrigerated with dry ice will be transported to the Microbiology Research Institute of Shenzhen People’s hospital. After extracting DNA from frozen fecal samples, 16S rRNA gene will be amplified by polymerase chain reaction (PCR) (v3-v4 hypervariable region) and sequenced using Illumina miseq platform. All data collection procedures will be performed following the local coronavirus disease 2019 (COVID-19) epidemic prevention and control policy.

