### Missing data

Retention of participants will be ensured during the monitoring period through the support of mothers, lactation encouragement and provision of psychological services. The following events are considered as follow-up losses: the study is not continued due to neonatal death, unstable clinical symptoms and other reasons; the intervention dose does not reach the expected 70%; and parents of preterm infants withdraws from the trial at any time. Eliminated or corrected observations and related reasons will be recorded for future reference.

Most types of missing data in the study will come from random missing. All missing data will be processed with SAS software using the double-robust inverse probability weighting method [53]. Its underlying principle is to estimate the weighted average of the outcome indicators of the complete data sample. Among them, the weight of each individual is the reciprocal of the probability that the outcome index of the individual is not missing, yielding an effect estimation closer to the real value.

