### Quality control

In clinical research, quality control should be carried out in the whole process of trial design, implementation and completion. In the design stage, to improve the quality of test data, a data monitoring committee (DMC) will be established. DMC will composed of the data verifiers (ZY and NW) and the principal investigators at each center (XY, RL and HP). The research team at each center will be composed of the principal investigator (XY, RL and HP), data quality controller (CC, LZ and ZY), syringe preparing nurse and the intervener. In the design phase, calculation of sample size, training of researchers, formulation of data management plan, and reasonable selection of efficacy observation indicators will be considered. The training will cover standardized operation process, including recruitment, randomization and web-based data collection. In the implementation phase, a standardized data collection process will be adopted, and the DMC will conduct regular verification of the filling of case report form (CRF) and research records at each center. Data verification will mainly focus on the following aspects: 1) the timeliness and completeness of data filling in CRFs, and the education on mother lactation to minimize data loss; 2) normalization of data filling; 3) records of adverse events, including the number and duration of adverse events during OAC, and records of colostrum intervention; and 4) monitor the progress of the study and verify the implementation of the study protocol, blind method performance and adverse events. After the study, the data will be collated, verified and statistically analyzed (including missing values, inclusion and exclusion criteria, and adverse events). The quality control process of the protocol is shown in Fig. 2.

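### Death, NEC and late-onset sepsis are recorded but lie outside both the adverse-event definition and the outcome list, so no stated safety comparison by arm covers them

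*Protocol article*

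**What the plan says.** All references are to the protocol article.

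- **Definition** (Quality control, text after Fig. 2): "Adverse events are defined as aspiration to the lungs, resuscitation due to severe bradycardia or apnea after intervention, and postnatal infection with cytomegalovirus", with the last item restricted to infection thought to come from fresh milk. Nothing marks the three items as examples.
- **Death** (Missing data): "The following events are considered as follow-up losses: the study is not continued due to neonatal death, unstable clinical symptoms and other reasons". The same sentence adds infants who received less than 70% of the planned dose and parental withdrawals.
- **Recording** (Data collection): "Descriptive and clinical data be collected from both groups". The items listed for the hospital stay include "NEC, LOS and mortality; and respiratory support".
- **Outcomes** (Outcomes and Table 1): the section opens "Primary outcome measures: 1a) a between-group difference in gut microbial alpha diversity". Every primary and secondary outcome concerns microbiota or metabolites.
- **Verification** (Quality control): one item checked is "records of adverse events, including the number and duration of adverse events during OAC". Adverse events are also named among the matters to be analysed after the study.
- **Committee review** (text after Fig. 2): "The DMC will conduct non-blind access to all data and discuss the results of the interim analysis, adverse events and compliance". This discussion is held with the trial steering committee, which decides whether the trial continues.
- **Safety claim** (Abstract, Discussion): "This proposal advocates for the promotion of OAC as a safe and relatively beneficial protocol in neonatal intensive care units".

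**The concern.** The Background treats NEC, LOS and death as the outcomes that matter most in these infants, and says that evidence for an effect of OAC on them is insufficient. The Abstract nevertheless presents OAC as safe.

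A reader would expect a safety assessment behind that claim to include these three events. The article instead fixes a definition that excludes them, and it files death with losses to follow-up. The term adverse events is the one used at each stated safety step, so the definition decides what those steps count. A report of few adverse events could then be correct under the definition and still say nothing about death, NEC or sepsis. The decision to continue the trial would follow a discussion whose named safety topic has the same gap.

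**Working it through.** The point rests on reading the sections against each other; no figure in the plan is in dispute.

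**Step 1. Where each event is placed.**

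| Event | In the adverse-event definition | Primary or secondary outcome | Recorded | Also classed as |
|---|---|---|---|---|
| Aspiration | yes | no | yes, as adverse event | – |
| Resuscitation for bradycardia or apnea after intervention | yes | no | yes, as adverse event | – |
| Milk-associated cytomegalovirus infection | yes | no | yes, as adverse event | – |
| Death | no | no | yes, as clinical data | follow-up loss |
| NEC | no | no | yes, as clinical data | – |
| LOS | no | no | yes, as clinical data | – |

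**Step 2. Which stated safety steps reach the last three rows.**

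- Verification of case report forms concerns adverse events, so it is bounded by the definition. One of its items refers to events during the five-day intervention, whereas NEC, LOS and mortality are recorded over the hospital stay.
- The interim analysis is of the primary endpoint, that is, the day-7 Shannon index and short chain fatty acids.
- The committee discussion covers interim results, adverse events and compliance. None of these topics contains death, NEC or LOS as defined.
- The final analysis names adverse events, again bounded by the definition.
- DMC access is to all data, so the three events are available to it. No comparison of them is stated.

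Taken literally, a death from sepsis or NEC adds one follow-up loss and one mortality record. It adds no adverse event unless a listed event also occurred in that infant.

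**Step 3. The loss allowance that deaths share.** Inputs from Sample size: 143 evaluable per arm, 10–12% loss, 160 randomised per arm.

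- The plan's figure reproduces: 143 / (1 − 0.10) = 158.9, rounded up to 159; 143 / (1 − 0.12) = 162.5, rounded up to 163. The chosen 160 lies between them and implies a loss of 1 − 143/160 = 10.6%, or 17 per arm and 34 in total.
- Applied to 320 infants, the stated range gives 0.10 × 320 = 32 to 0.12 × 320 = 38.4.
- Deaths, instability, under-dosing and withdrawals are pooled here, so the figure says nothing about the number of deaths.

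**Step 4. Illustration with assumed counts.** The article gives no rates of death, NEC or LOS.

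- 19 versus 8 deaths among 160 per arm: two-sided Fisher p = 0.043.
- 24 versus 12 NEC cases among 160 per arm: p = 0.0504, just above 0.05.
- In both cases these events would add 0 versus 0 to the adverse-event count. That restates the definition and is not an estimate of harm.
- With 160 per arm, power is about 40% for assumed rates of 5% versus 10%, and 71% for 10% versus 20%. A table by arm would therefore serve monitoring and description rather than a confirmatory test.

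**The case against.** A reader might infer that an excess of deaths, NEC or sepsis would appear in no safety count, or would be hidden. The article does not support that reading. The three events are recorded in both arms. The DMC has unblinded access to everything. The Ethical and dissemination section requires safety reports, together with the DMC's safety review data, to go to the ethics committee, and neither is limited to the three listed items. Classing a death as a follow-up loss explains why later stool samples are absent; it does not remove the mortality record, and reasons for eliminated observations are to be kept.

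Two further arguments deserve weight. First, this is a condensed article, and table layouts, safety populations and a DMC charter are commonly left to fuller documents; their absence here is not a fault. Second, treating frequent complications of prematurity as clinical outcomes rather than adverse events is a legitimate choice, especially where the intervention is hoped to reduce them.

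These arguments defeat the strong reading and reduce the severity. They do not remove the point. The closed definition and the classing of death are stated rules, not matters left open. The article also does not take the alternative route, because it does not name the events as clinical outcomes either. Access to data makes detection possible but is not a planned comparison.

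**Conclusion.** The point holds in a limited form and should be fixed. As stated, the adverse-event verification, the named topics of the committee discussion and the final adverse-event analysis leave out death, NEC and LOS, although all three are collected in both arms. The DMC could still notice an imbalance. A safety conclusion built on the stated definition would not cover these events, and the Abstract's description of OAC as safe could not rest on it for them.

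No numerical size can be given: the event counts and rates in the illustration are assumptions, and the loss allowance does not isolate deaths. The primary endpoints, sample size and efficacy tests do not depend on this point. The conclusion assumes that adverse events carries the stated definition wherever the article uses the term, and that no fuller document overrides it.

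**What to change.** Reconcile three sections.

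1. **Text after Fig. 2 in Quality control:** state that death, NEC and LOS are safety events or, if the sponsor prefers to keep the three-item definition, clinical safety outcomes reviewed alongside it. Say that they are tabulated by arm for the DMC and in the final report, for all randomised infants, whatever their dosing or follow-up-loss status. This agrees with the intention-to-treat approach in Statistical analysis.
2. **Missing data:** report death as an event by arm, and not only as a reason for loss to follow-up.
3. **Data collection:** note that the recorded NEC, LOS and mortality items feed that table.

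The cost is a few sentences and one table. The data are already collected, so no new procedure is needed, and the table can include infants already enrolled. The small downside is that expected events of prematurity will appear in the safety table; with both arms side by side they can be read in context.

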### Inclusion/exclusion criteria

Inclusion criteria: 1. gestational age less than 32 weeks and birth weight less than 1500 g; 2. admission to NICU ≤ 24 h; and 3. be able to start the agreement within 72 h of birth.

Exclusion criteria: 1. birth asphyxia (defined as umbilical artery / first hour arterial PH < 7.0 or cardiopulmonary resuscitation in the delivery room); 2. birth complicated by severe gastrointestinal malformations (such as intestinal atresia, esophago-tracheal fistula, intestinal rotation abnormalities, congenital megacolon); 3. prenatal diagnosis of congenital chromosomal abnormalities or suspected congenital genetic metabolic diseases; and 4. maternal drug abuse or contraindications to breastfeeding (HIV and cytomegalovirus infection).

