### Collection of milk and oropharyngeal administration procedure

Obstetric nurses will encourage the mother of each newborn to start lactation within 24 h of delivery and educate them on breast massage and electric breast suction every 3 h. Mothers of preterm infants will be encouraged to milk frequently with hygienic hands to ensure a steady supply of breast milk. To ensure the feasibility of oropharyngeal administration of mother’s milk to preterm infants in the treatment group, the mother’s milk will be collected in a pre-labeled sterile milk collection bag. A minimum colostrum volume of 1.6 ml will be collected and stored in the breast milk refrigerator of NICU. After ascertaining that baby's information is consistent with details in the label on the breast milk storage bag, an on-site investigator (nurses preparing syringes) will select the storage bag with the latest lactation time and use sterile gloves and syringes to suck 0.1 ml of colostrum or sterile water for oropharyngeal administration, and cover them with opaque tape and needle cap. Each syringe will be labeled with serial number, hospitalization number, name and date. Then, the bag will be stored at 0 ~ 4℃ for 24 h for subsequent intervention. In this study, all other storage bags will be stored in a freezer at -18 °C until the infant begins enteral feeding.

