In the first 48–72 h the treatment group will receive the treatment measures: two 1 mL sterile syringes each aspirated with 0.1 mL of colostrum, placed at room temperature for 5 min. The colostrum will be maintained at room temperature for OAC use. After removing the tip and cap of the first syringe, the colostrum will be slowly injected along the right oral mucosa for at least 20 s. Then, the right buccal mucosa will be wiped with a sterile cotton swab for at least 10 s. The second syringe will be used in the same way on the left oral mucosa. The procedure will be performed every three hours for five days. The control group will be treated with sterile water following similar operation steps. Colostrum for the control group will be frozen in the NICU breast milk refrigerator for enteral feeding. Vital signs will be monitored throughout the process, including heart rate, respiration, body temperature and pulse oxygen saturation. During treatment, newborns will be regularly monitored and observed. If their clinical symptoms are unstable (heart rate is greater than 200 or less than 100, breathing is greater than 80, or the oxygen saturation is maintained above 85% only when the oxygen concentration increases by 10%) [44], the intervention will be interrupted. Once the clinical situation stabilizes, the treatment will be resumed immediately, and the final intervention dose and adverse reactions recorded.

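### Postnatal cytomegalovirus counts as an adverse event only if attributed to fresh milk, an exposure tied to the OAC arm during the intervention, so equal infection rates can yield unequal counts

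*Protocol article*

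**What the plan says.** The text after Fig. 2, in the Quality control section of the protocol article, lists three adverse events. The third is "postnatal infection with cytomegalovirus thought to be associated with fresh breast milk". It does not name who makes this judgement, and it sets no period.

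The section on milk collection and oropharyngeal administration fixes how milk is handled:

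- **OAC arm.** Syringes are filled from the most recently expressed bag. "Then, the bag will be stored at 0 ~ 4℃ for 24 h for subsequent intervention".
- **Remaining bags.** "all other storage bags will be stored in a freezer at -18 °C until the infant begins enteral feeding".
- **Control arm.** "The control group will be treated with sterile water following similar operation steps", and "Colostrum for the control group will be frozen in the NICU breast milk refrigerator for enteral feeding".

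Two other statements bear on the point. The exclusion criteria include "maternal drug abuse or contraindications to breastfeeding (HIV and cytomegalovirus infection"). The Randomization section states: "The subjects, intervention nurses, the principal investigator and the data verifier will be blinded". However, the Quality control section forms the data monitoring committee (DMC) from the data verifiers and the centre principal investigators, and gives it unblinded access to all data.

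**The concern.** A safety event should be defined so that the same infection in two infants is counted the same way whichever arm they are in. Here the definition includes a judgement about cause, and the cause it names is close to the randomised treatment itself. An OAC infant with postnatal CMV has a documented exposure to unfrozen milk during the intervention. A control infant with the same infection has no such scheduled exposure in that period, so the infection may never become an adverse event.

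The DMC and the trial steering committee discuss adverse events, and the steering committee decides whether the trial continues. A count that partly reflects allocation could make OAC look less safe than it is. If attribution is instead made without knowledge of the arm, real infections are lost from the safety record of both groups.

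**Working it through.** **Inputs from the protocol article.** 160 infants per arm (Sample size). The attribution condition (Quality control, after Fig. 2). Unfrozen milk scheduled only for OAC during the intervention (milk collection and administration section).

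**Check of the plan's own figure.** A difference of 0.2 with SD 0.6, two-sided 0.05 and 80% power gives 142.2 per arm by the t-based calculation, rounded up to the stated 143. Allowing for loss, 143 / 0.90 = 158.9 (159) and 143 / 0.88 = 162.5 (163). The stated 160 lies in that range, so it is used below.

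**Assumptions.** The document gives no CMV rate. Let r be the true postnatal CMV rate, equal in both arms. Let a1 and a0 be the proportions of infections attributed to fresh milk in the OAC and control arms.

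**Formulas.**

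- Expected counted events: OAC = 160 × r × a1; control = 160 × r × a0.
- Artificial gap in percentage points: 100 × r × (a1 − a0). It is zero when a1 = a0.

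**At r = 5%** (160 × 0.05 = 8 true infections per arm):

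| Attribution, OAC v control | Counted events | Gap |
|---|---|---|
| 50% v 50% (blinded judge) | 8 × 0.5 = 4 v 8 × 0.5 = 4 | 0 points |
| 80% v 40% (partial knowledge) | 8 × 0.8 = 6.4 v 8 × 0.4 = 3.2 | 2 points |
| 100% v 0% (attribution follows intervention exposure) | 8 v 0 | 5 points |

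Fisher's exact test on 8/160 v 0/160 gives p = 0.007. On the rounded middle row, 6/160 v 3/160, it gives p = 0.50.

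**Other assumed rates.**

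- r = 2%: 1.6 v 1.6, then 2.6 v 1.3, then 3.2 v 0. The last, rounded to 3 v 0, gives p = 0.25.
- r = 10%: 8 v 8, then 12.8 v 6.4, then 16 v 0. The last gives p < 0.001.

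The true difference is zero in every row.

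**The no-gap row.** With 50% attributed in each arm the comparison is balanced, but 8 true infections per arm have become 4. The clause then discards half of the events.

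**Under the fix.** Counting every infection sets a1 = a0 = 1. Expected counts are 3.2 v 3.2, 8 v 8 and 16 v 16 at 2%, 5% and 10%.

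**The case against.** The strongest reply is that nothing shows attribution will follow the arm. Several parts of it stand.

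- **Blinding.** A reader might infer that the rule always creates an arm difference. It does not: a judge who cannot tell the arms apart attributes equally and produces no gap, and the principal investigator and data verifier are declared blinded. The protection is weak, because those same roles make up the unblinded DMC and the article names no separate assessor.
- **Later feeding.** The definition refers to fresh milk in general, not study colostrum, and has no time limit. Other bags are frozen only until enteral feeding begins, and the article does not say whether later milk is fresh or frozen. Control infants could qualify later, so the 100% v 0% row is an extreme and not a forecast. Also, the article does not define fresh; reading it as unfrozen is an inference from the handling rules.
- **Base rate.** Excluding maternal CMV infection should lower the rate in both arms. Counts may be small, and at 2% even the extreme row is only about 3 v 0.
- **Window.** A reader might infer from "the number and duration of adverse events during OAC" that only events in the five-day course are counted. The text does not support this. The phrase is introduced as an example of what the records include, the next item on the same list mentions adverse events without a window, and adverse events are analysed again after the study.
- **Validity.** A reader might conclude that the between-arm safety comparison is invalid. That goes too far: CMV is not a listed outcome, and no between-arm test of it is specified.

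It can also be said that a condensed article leaves causality assessment and detailed variable definitions to fuller documents. That is fair for who judges and over what period. It does not answer the main point, because the attribution condition is stated here as part of the definition.

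**Conclusion.** The concern holds as a weakness in a stated definition. Making attribution to fresh milk a condition for counting CMV ties the event to an exposure that, during the intervention, is scheduled for one arm only. The definition can create an arm difference under equal true rates if the person attributing cause knows exposure or allocation; under true blinding it loses infections from both arms instead. Neither result is wanted, and randomisation makes the clause unnecessary: with all infections counted, any excess due to OAC appears in the comparison itself.

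The size cannot be fixed from the document. At an assumed 5% rate the artificial gap ranges from 0 to 5 percentage points, depending wholly on attribution proportions that are also assumed. The p-value of 0.007 belongs to the extreme case alone. The point affects safety reporting and leaves the primary outcomes and the sample size untouched.

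**What to change.** Define the event as any diagnosed postnatal CMV infection, counted identically in both arms over one stated window, for example from first dose to day 28, the last planned stool sample. Record the suspected source as a separate field, preferably completed by an assessor blinded to allocation, and do not make it a condition for counting. Relatedness can still be reported beside the total.

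The cost is a change of wording and one case report form field, with no extra testing. The downside is that some infections unrelated to study milk will be counted, equally in both arms.
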